### 3.2 Statistical analysis

Shapiro-Wilk and Kolmogorov-Smirnov tests will be used to check the normality of the distribution. As a rule, the distribution of free carnitine and acylcarnitines concentrations in whole blood differs from normal (Manta-Vogli et al., 2020). If the data sets show a normal distribution, M (mean) and standard deviation (error of the mean) will be used for descriptive statistics of the samples. Parametric tests will be used to test for differences between AA and AC concentrations depending on various factors (gender, place of residence) (t-test, analysis of variance (ANOVA) with or without Tukey’s test). If the data sets do not show a normal distribution, Me (median) and quartiles (interquartile range IQR) will be used for the descriptive statistics of the samples. Non-parametric tests (Mann-Whitney U-test, Kruskal-Wallis H-test without or with subsequent *post hoc* comparisons using U-test will be applied to test the differences mentioned above. The Pearson χ^2^ criterion will be applied to identify intergroup differences for categorical variables. If the distribution of analytes is skewed, reference intervals in the healthy control group will be determined nonparametrically and correspond to the 0.5–99.5th percentile of the experimental distribution. Correlations between body weight, and concentration of each analyte will be performed using corresponding tests.

Indices of sensitivity (Sn), specificity (Sp), positive predictive values (PPVs), and negative predictive values (PVN) will be calculated for each diagnostic test under consideration. PPVs will be calculated by dividing the total number of true positive cases by the total number of true positive and false positive cases. The detection rate will be calculated by dividing the number of cases diagnosed by the number of screened children with suspected metabolic disorders. Multiple linear regression coefficients will be calculated to assess the relationship of each analyte with the factors of gender, weight, and place of residence. Due to the number of variables subjected to analysis, and the anticipated presence of multiple outcomes, the included tests may not be sufficient. So, the cluster analysis and, possibly, the decision-tree method will be applied. Decision trees break down complex data into more manageable parts, beneficial in prediction analysis, data classification, and regression. A dimensionality reduction method, principal component analysis (PCA), will also be applied. Two-sided levels <0.05 are assumed to be statistically significant. Statistical analysis will be carried out using the statistical packages IBM SPSS v. 23.0 (IBM, Armonk, NY, United States), Statistica (StatSoft, Inc., Tulsa, OK, United States, v. 10), and R 3.3.2 (R Foundation for Statistical Computing, Vienna, Austria.)

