### 2.3 Methods and procedures

#### 2.3.1 Mass spectrometry analysis. specimen collection and storage

Neonatal whole blood samples are taken from high-risk and healthy infants no earlier than 3 h after feeding by heel prick with a heel stick. Five drops of whole blood (∼75 µL each) are put onto Guthrie cards, Ahlstrom 226 filter paper, PerkinElmer 226 Five-Spot Card (PerkinElmer Health Sciences, Greenville, United States) to form dry blood spots (DBSs) for LC-MS/MS analysis. The sample must be taken before transfusion therapy or extracorporeal membrane oxygenation. If the sample was not taken before the administration of transfusion agents, blood should be taken no earlier than 48–72 h after the transfusion.

Whole blood samples from older children at high-risk and healthy children are collected after 4-hour fasting using a standard venipuncture method. The DBS card is prepared by applying five drops of whole blood (each ∼75 μL) to the Guthrie cards, Ahlstrom 226 filter paper, PerkinElmer 226 Five-Spot Card (PerkinElmer Health Sciences, Greenville, United States).

Samples must be dried for 4 h at room temperature and then stored at 4°C in individually labeled zippered plastic bags with desiccants or other sealed containers until analyzed by LC-MS/MS by standards of the Institute of Clinical and Laboratory Standards (CLSI, 2013). Samples must be sent to the laboratory within 5 days. In case of long-term storage of samples, it will be carried out at a temperature of −20°C. Cut-off values will be set according to the manual for the Neobase2 TM Non-derivatized MSMS kit (PerkinElmer, Wallac Oy, Turku, Finland). They will be adjusted over time as the number of samples increases.

If metabolite concentrations in dry blood spot samples exceed the cut-off values, the LC-MS/MS test will be repeated using the same dried blood spot sample the next day. If the test results show persistent abnormal results, the child will be further examined. Blood and urine are used to confirm the diagnosis. Diagnosis is confirmed by urine organic acid analysis, plasma amino acid analysis, or direct enzyme analysis. Duplicate samples are stored frozen at −20°C with a desiccating agent.

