#### 2.3.4 Diagnosis of targeted diseases (conditions)

The diseases to be analyzed in this study include AAD, OA, and FAOD, which are detected by measuring acylcarnitines, succinylacetone, and amino acids with MS/MS. For their diagnosis, the ratios of Phe/Tyr, C3/Met, C3/C2, C3/C0, С14:1/С2, С14:1/С16, С14:1/С12:1, С0/(С16+С18), and (C14 + C14:1 + C16:1)/C0 will be set. IEMs subject to diagnosis are displayed in Table 3. Limit values will be determined by studying levels of amino acids, acylcarnitines, and succinylacetone in DBSs of 750 healthy children in western Kazakhstan. In the case of normally distributed data, the cut-offs will be set to four standard deviations (SD) above or below the mean. If the distribution of analytes is skewed, reference intervals in the healthy control group will be determined nonparametrically and correspond to the 2.5–97.5th percentile of the experimental distribution. All cut-offs are subject to adjustment in light of further analyzes and additional clinical data.

**TABLE 3 T3:** Primary and repeated LC-MS/MS screening and confirmatory IEM tests.

Disorder	Primary and repeated LC-MS/MS screening	Confirmatory tests
AMINO ACIDS & UREA CYCLE DISORDERS		
PKU	↑Phe, ↑Phe/Tyr ratio	↑Phe, Phe/Tyr ratio (Blood)
		↑Phenyl acetic acid (Urine)
		Genetic sequencing of the PAH gene
MSUD	↑Val, Ile, Leu	↑Val, Ile, Leu (Blood)
	↑ Leu/Ile	↑Val, Leu/Ile, Leu/Phe ratio (Blood)
	↑Leu/Phe	↑α-KG, 2OH-IVA (Urine)
	↑Xle/Ala	Genetic sequencing of the BCKDHA, BCKDHB genes
	↑Xle/Phe	
	↑Val/Phe ratio	
HCU	↑Met, Hcy	↑Met, Hcy (Blood)
	↑Met/phe ratio	
CIT I	↑Cit	↑Cit (Blood)
		↑OA (Urine)
		Genetic sequencing of the ASS1 gene
ASA	↑Argininosuccinic acid	↑Argininosuccinic acid (Blood)
		↑Argininosuccinic acid (Urine)
		Genetic sequencing of the ASL gene
OTCD	↓Cit ↑Orn	↓Cit (Blood)
		↑ Glu (Blood)
		↑Orotic acid (Urine)
		Genetic sequencing of the OTC gene
CPS	↓Cit	↑Organic acids (Urine)
		Genetic sequencing of the CPSI gene
NAGSD	↓Cit	↓Cit (Blood)
		Genetic sequencing of the NAGS gene
TYR I	↑Tyr ↑Tyr/Phe ratio	↑ Cit (Blood)
		↑ SuAc (Urine)
		↑ OA (Urine)
		Genetic sequencing of the FAH gene
TYR II	↑Tyr	Normal levels succinylacetone (Urine)
		Genetic sequencing of the TAT gene
NKHG	↑Gly	↑Gly (Blood)
		↑Gly (CSF/P)
ARG	High arginine ↑Arg/Orn	High plasma arginine and high urinary orotic acid
ORGANIC ACID DISORDERS		
SBCAD	↑С5	Genetic sequencing of the ACADSB gene
MMA	↑C3	↑C3, C3/C2 ratio (Blood)
	↑C3/C2 ratio	↑MMA, 3OH-PA, MCA, PG (Urine)
	↑C4DC, C3/C0	

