#### 3.2.1 Descriptive statistics and group comparison

Descriptive statistics and reference intervals for whole blood concentrations of 15 AAs, 35 ACs, and SuAc in healthy children divided into subgroups according to gender will be presented in tables. For each analyte in the healthy control group, the upper cut-off will be set above the 97.5^th^ percentile, while the lower cut-off will be set below the 2.5th percentile. Differences in the distribution of amino acids, acylcarnitines, and succinylacetone between groups, as determined using the Mann-Whitney and Kruskal-Wallis tests, will be noted in the table if found.

Cut-off values for analytes and their ratios for selective screening of AAD, OA, and FAOD presented in Table 3 will be pointed out. The results of determining the analytes in DBS in children of the healthy control group will be compared with those of previously published studies in other populations. According to the inclusion criteria, healthy newborns in the reference group must be full-term (born at 37–42 weeks). However, it should be taken into account that some of the newborns at risk for IEM are born prematurely. In this regard, it is also necessary to determine reference intervals for the concentrations of 15 AAs, 35 ACs and SuAc in dried blood spots of premature infants who do not have clinical symptoms of IEM.

Comparison of mean concentrations (Me, range) of analytes between groups of high-risk children and healthy controls will be presented.

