### 3.5 Presenting positive and false positive cases

Even though the number of false positive results during LC-MS/MS is much lower than when using standard biochemical tests and, according to different researchers, ranges from 1.9% to 2.3% (Selim et al., 2014; Hassan et al., 2016), we assume that a certain number of samples will turn out to be a false positive. The number of true and false positives for each disease according to each disorder after the primary (baseline) LC-MS/MS will be established. Positive predictive values will be calculated by the total number of true positive cases divided by the total number of true positive and false positive cases.

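### The limits that define an abnormal metabolite value are stated inconsistently: 2.5–97.5th against 0.5–99.5th percentile for skewed analytes, and mean ±4 SD against 2.5th/97.5th percentile for normal ones

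*Protocol article*

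**What the plan says.** Four sections of the protocol article set limits for the 51 metabolites.

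- **Section 2.3.1:** "Cut-off values will be set according to the manual for the Neobase2 TM Non-derivatized MSMS kit". The next sentence adds: "They will be adjusted over time as the number of samples increases".
- **Section 2.3.4:** "Limit values will be determined by studying levels of amino acids, acylcarnitines, and succinylacetone in DBSs of 750 healthy children in western Kazakhstan". If the data are normal, "the cut-offs will be set to four standard deviations (SD) above or below the mean". If they are skewed, "reference intervals in the healthy control group will be determined nonparametrically and correspond to the 2.5–97.5th percentile of the experimental distribution". The section then leaves all cut-offs open to later adjustment and gives no criterion.
- **Section 3.2:** for skewed analytes, "reference intervals in the healthy control group will be determined nonparametrically and correspond to the 0.5–99.5th percentile of the experimental distribution".
- **Section 3.2.1:** with no condition on the distribution, the upper cut-off for each analyte lies above the 97.5th percentile of the healthy group and "the lower cut-off will be set below the 2.5th percentile".

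Table 5 in Section 3.3 has one column for the cut-off limit and another for the reference range. The text does not say which rule fills which column.

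**The concern.** Two pairs of statements cannot both be followed as they stand. For a skewed analyte, Sections 2.3.4 and 3.2 use the same sentence to define the same reference interval with different percentiles. For a normal analyte, Section 2.3.4 goes out to four standard deviations, while Section 3.2.1 names the 2.5th and 97.5th percentiles for all analytes. Nothing says which section prevails, or at what point the kit-manual values give way to values from the 750 controls.

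These limits drive the main results. Normal and abnormal values are the first primary outcome in Section 3.1, and the number and proportion of children with abnormal values is the second. Sections 2.3.1 and 2.3.5 use the limits to trigger the repeat test and the referral for confirmation. Sections 3.2 and 3.5 build false positives and predictive values on the result. Two analysts working faithfully from this text could report different reference values, proportions abnormal and PPVs from the same data.

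**Working it through.** The protocol states no target flag rate or specificity, so there is no figure of its own to reproduce. The check is the nominal share of healthy children that each rule leaves outside its limits.

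**Inputs.** Percentiles and SD multiple: Sections 2.3.4, 3.2 and 3.2.1. Healthy controls: 750 (Sections 2.1 and 2.3.4). Panel: 15 amino acids, 35 acylcarnitines and succinylacetone, 51 in all (Section 2.1).

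**Formulas.** Percentile limits: lower tail plus upper tail. Mean ±4 SD for a normal analyte: 2 × (1 − Φ(4)). Expected number outside per analyte: 750 × share.

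| Rule | Section | Applies to | Share outside | Expected among 750 controls |
|---|---|---|---|---|
| 2.5–97.5th percentile | 2.3.4 | skewed | 0.025 + 0.025 = 5% | 37.5 |
| 0.5–99.5th percentile | 3.2 | skewed | 0.005 + 0.005 = 1% | 7.5 |
| mean ±4 SD | 2.3.4 | normal | 2 × 0.00003167 = 0.0063% | 0.05 |
| 2.5th/97.5th percentile | 3.2.1 | every analyte | 5% at those percentiles, less if further out | up to 37.5 |
| kit manual | 2.3.1 | not stated | cannot be computed from the document | – |

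**Skewed analytes (2.3.4 against 3.2).** 0.05 / 0.01 = 5-fold. One-sided, 0.025 / 0.005 gives the same ratio.

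**Normal analytes (2.3.4 against 3.2.1).** 0.05 / 0.00006334 = 789-fold if the Section 3.2.1 cut-off sits at the named percentiles. One-sided, 0.025 / 0.00003167 gives the same ratio. On the measurement scale the limits lie at ±1.96 SD and ±4 SD.

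**Which ratio matters more.** Section 3.2 says that free carnitine and acylcarnitines as a rule depart from normality. On the protocol's count, acylcarnitines are 35 of 51 analytes (35/51 = 69%). The 5-fold difference is therefore the working figure for most of the panel. The 789-fold figure concerns only analytes judged normal.

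**Precedence.** Read side by side, the four sections contain no sentence that ranks them, limits one to a phase of the study, or ends the adjustment allowed in Sections 2.3.1 and 2.3.4.

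**The case against.** The case on the other side has real substance.

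- A reader might count four mutually incompatible rules. That goes too far. Within Section 2.3.4 the ±4 SD and percentile rules are alternatives for different distributions, and the kit-manual values read as a starting point.
- Section 3.2.1 places cut-offs above and below its percentiles. Read literally, these are bounds, 5% is a ceiling, and a ±4 SD cut-off would satisfy them. This reading can dissolve the conflict for normal analytes. It then leaves Section 3.2.1 without a definite cut-off and does not touch the conflict between Sections 2.3.4 and 3.2.
- Table 5 separates cut-off limit from reference range, so it would be too strong to say that the plan treats them as one thing. The text still assigns no rule to either.
- Repeat and confirmatory tests sort true from false positives. That limits the harm to first-tier positives and to children never sent on, but both depend on the limits.

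Other inferences are tempting but unsupported:

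- *Most healthy children would be flagged on at least one of 51 analytes.* This needs an assumption about correlation and a definition of positivity that the plan does not use. Section 3.2 computes predictive values per test, and Section 3.5 counts positives per disease.
- *The plan expects 1.9% to 2.3% false positives.* Section 3.5 attributes that range to other researchers and sets no target.
- *Low markers could never be flagged under mean −4 SD.* This needs a coefficient of variation of at least 25%, which the document does not give. Free carnitine is expected to be non-normal, so Section 2.3.4 would send it to percentiles.
- *The 0.5th percentile cannot be estimated.* This rests on age-by-sex cells of 125 that the document never defines.

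**Conclusion.** The point holds. For skewed analytes the contradiction is direct: the same sentence carries limits that leave a nominal 5% or 1% of healthy children outside, a 5-fold difference affecting most of the panel. For normal analytes there is a second conflict, about 789-fold, on the assumption that the Section 3.2.1 cut-off sits at its named percentiles and the analyte is truly normal. The kit-manual values are a further source that is not reconciled, of unknown size.

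The rates are nominal rates in healthy children. The document does not give the analyte distributions in the symptomatic children to be screened, so the effect on their false positives and PPV cannot be quantified from it. The direction is clear: wider limits mean fewer first-tier positives and fewer children sent on.

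This is not detail that an article may leave to a fuller document, because the article states conflicting numbers. It should be corrected before either primary outcome is analysed. The document does not show which limits are intended.

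**What to change.** 1. Reconcile Sections 2.3.1, 2.3.4, 3.2 and 3.2.1.
2. State one definition of the reference interval and, separately, one definition of the decision cut-off, and link each to its column in Table 5. The choice of values is the sponsor's.
3. Label the kit-manual values as interim and say when they cease to apply.
4. Fix the final cut-offs once the 750 controls are complete. Reclassify all stored screening results with that one set before computing the proportion abnormal, false positives and PPV.

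The cost is wording in four sections and one re-run of stored results, with no additional children. The drawback is that the reported cut-offs may differ from those used early in recruitment, which the report should state.

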### 2.2 Selection of subjects

#### 2.2.1 Sample size estimation

When calculating the sample size for the upcoming project on selective screening, we relied on published similar studies. Researchers pointed out the following essential factors contributing to the sample size calculation: Daniel’s formula for prevalence studies in case of expanded screenings, the reported frequencies of different IEM within the studied populations, and the number of infants born in the country during the period of interest (Yoon et al., 2005; Golbahar et al., 2013; Hassan et al., 2016; Shibata et al., 2018; Sarker et al., 2019; Manta-Vogli et al., 2020). Notably, many researchers corrected their calculations, considering the situation with consanguineous marriages in their country.

According to the review by Shibata N et al., the IEM overall detection frequency was 3.0% (1.2% in Japan and 9.2% in other Asian countries) (Shibata et al., 2018). Yoon et al. reported 5.4% IEM among South Korean annual births (Yoon et al., 2005). Of these data on IEM frequency throughout Asian countries, Mongolian values (1.6%) have attracted our attention due to the similar nomadic history and way of life where consanguineous marriages were strictly forbidden (Shibata et al., 2018). Along with that, the Mongolian index does not include all types of IEM except the most distributed.

Based on mentioned factors, we requested data on the number of childbirths across the four provinces (oblasts) of western Kazakhstan within 3 years before the project started. The average rate of infants born alive annually ranged between 69–73,000 (https://stat.gov.kz/en/industries/social-statistics/demography/publications/). Thus, we have decided to build on the IEM average frequency of 2%–2.5% and determined the expected sample size of 1,500 children for selective screening with 750 healthy controls.

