**FIGURE 2 F2:**
[figure not shown]
Sites for data collection throughout western Kazakhstan.

Children from the western Kazakhstan population with suspected metabolic disorders are examined for congenital metabolic disorders and referred by primary care neonatologists and pediatric consultants between October 2022 and August 2024 based on their clinical symptoms associated with metabolic disorders. The study includes newborns and children being treated in maternity wards and pediatric clinics of 7 pediatric hospitals in the region. Patients with suspected IEM from all sites are referred to the Regional Tertiary Care Center or the Mother and Infant Health Center in Aktobe, or their samples are sent from other involved hospitals. Patient information is obtained from the Individual Registration Cards (IRCs) completed by study participants. The completed questionnaires are checked by the researchers. In case of improper collection, data must be removed from the study if it is impossible to check adequately. The IRC sample and other supplementary materials are placed in the *clinical. trials.gov* Register (https://www.clinicaltrials.gov/study/NCT05910151) and a publicly available repository (https://osf.io/cmrh7/).

To set reference values of 15 AAs, 35 ACs, and SuAc, healthy participants without any disease are included in the study. A total of 750 healthy male and female children aged 1 day to 18 years are recruited based on random selection. Participants will be balanced by gender and place of residence. Considering the distribution of urban and rural populations in western Kazakhstan, approximately half of them will be selected in urban areas, the other half in rural areas. A summary of the age, gender, and geographic distribution of study participants will be presented in Table 1.

**TABLE 1 T1:** Demographic data to be collected on study participants.

Variables	Selective screening (n = 1,500)	Healthy children (n = 750)
Age in days, years (median, range)		
Weight in grams, kilograms (median, range)		
Gender		
Male, n		
Female, n		
Geographic distribution		
Aktobe province		
Atyrau province		
West Kazakhstan province		
Mangystau province		
Urban population		
Rural population		

Screened children with positive first-level LC-MS/MS test results will be referred for second-level screening.

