#### 2.3.5 Confirmatory tests

Patients will be immediately referred for confirmatory tests if the results exceed the thresholds. A reanalysis of the same sample will be performed if the results fall outside the threshold. Patients will be referred for confirmatory tests if the second test also falls outside the threshold.

Confirmatory tests include:

Clinical data; analysis of therapeutic effects; reanalysis LC-MS/MS; urine analysis for organic acids by gas chromatography-mass spectrometry (GC-MS); amino acid analysis; routine blood test; blood biochemistry; blood gas analysis; tests for glucose and ammonia in the blood; tests for homocysteine, lactate and pyruvate in the blood; tests for acetone in the urine; biotin, biotin enzyme profile; measurement of enzyme activity; tests for gene mutations; DNA analysis; magnetic resonance imaging of the brain and electroencephalography.

As known, gas chromatography-mass spectrometry is one of the best methods for diagnosing congenital acidemia. As organic acids are practically not reabsorbed in the renal tubules, their concentration in urine is higher than in the blood, and they are easier to determine in urine. Patients with a positive dry blood spot test result using TMS with or without clinical manifestations of IEM will have urine organic acids determined by gas chromatography-mass spectrometry.

To determine organic acids in urine using GC-MS, collecting 10–15 mL of morning urine in a clean, dry container without preservatives and transporting it in a thermos with food ice is necessary. The urine can be frozen and stored at a temperature of −20 C0 until analysis (Gallagher et al., 2018).

Before collecting urine, appropriate instructions regarding fluid intake, consumption of certain foods, avoidance of certain medications, etc., should be followed.

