Dried blood spots or whole blood can be used for whole exome sequencing. When using whole blood: collect 2–5 mL of the patient’s blood into tubes with EDTA preservative (purple cap); carefully invert the tubes several times to mix with the preservative, but do not shake to avoid hemolysis. Transport in a thermos with food ice can be frozen and stored at a temperature of - 80 C0. Whole blood must be delivered no later than 7 days after collection.

To conduct whole-exome sequencing of human DNA using NGS technology, sequencing platforms, a sequencer, an automatic station for DNA extraction, a fluorimeter, a centrifuge, a laminar flow cabinet, a flow-through bactericidal air recirculation, a fridge, nucleic acid quantitation instrument; nucleic acid quality analyzer; thermal cycler; vortex spot; ultrasonicator; standard laboratory supplies (pipettes, 96-well plates, centrifuge tubes) are needed.

This procedure is carried out by the institution’s approved standard operating procedures and the NGS protocol guidelines of the technology used and includes three stages:Stage I: Preparation of the library. Preparing the library consists of the following steps: DNA sample extraction, PCR amplification of DNA, and library cleaning.Stage II: Sequencing: reading the obtained information from the biochip and transferring the data to the software. Studies use the NovaSeq™ 6,000 Sequencing System (Illumina, Inc.).Stage III: Bioinformation analysis: a bioinformatic analysis of the obtained data and laboratory interpretation of the results are being carried out (Fernandez-Marmiesse et al., 2018; Marshall et al., 2020; Austin-Tse et al., 2022).

Table 3 presents the criteria for primary and repeated LC-MS/MS screening for IEM and confirmatory tests.

The tests will be conducted in the INVITRO laboratory (Kazakhstan, Almaty) by ICH E-6 Guidelines for Good Clinical Practice. The INVITRO laboratory is accredited to determine the profiles of acylcarnitines, succinylacetone, and amino acids by LS-MS/MS analysis by ISO 15189. From October 2022 to August 2024, the frequency of 37 AAD, OA, and FAOD will be assessed using LC-MS/MS technology in a group of children at high risk. A summary report on screening high-risk children for IEM in western Kazakhstan by LC-MS/MS will be presented.

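### Sensitivity and NPV are promised, but only children with out-of-range LC-MS/MS results are verified, so neither index can be estimated for the screen

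*Protocol article*

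**What the plan says.** All passages are in the protocol article.

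- **Promise (3.2).** "Indices of sensitivity (Sn), specificity (Sp), positive predictive values (PPVs), and negative predictive values (PVN) will be calculated for each diagnostic test under consideration". Formulas follow only for PPV and for the detection rate.
- **Who is verified (2.2.2).** "Screened children with positive first-level LC-MS/MS test results will be referred for second-level screening".
- **Who is verified (2.3.5).** "Patients will be referred for confirmatory tests if the second test also falls outside the threshold". The same section reserves urine organic acid analysis for children with a positive dried blood spot.
- **Who is verified (2.3.1 and 3.1).** Section 2.3.1 reserves further work-up for persistently abnormal results. The second primary outcome in 3.1 ties retesting and confirmation to results beyond the thresholds.
- **Design (2.1).** Cross-sectional. No follow-up of screen-negative children is described.
- **Numbers.** Section 2.2.1 assumes an IEM frequency of 2–2.5% and "determined the expected sample size of 1,500 children for selective screening with 750 healthy controls". Under 2.3.5, "the frequency of 37 AAD, OA, and FAOD will be assessed using LC-MS/MS technology in a group of children at high risk". Section 3.5 plans counts of true and false positives for each disease.
- **Cut-offs (2.3.4).** "All cut-offs are subject to adjustment in light of further analyzes and additional clinical data".

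**The concern.** Sensitivity is TP/(TP+FN) and NPV is TN/(TN+FN). Both need FN, the number of affected children whom the screen passed as normal. The work-up rule yields a disease verdict only for children whom the screen flagged. This is complete verification of positives and none of negatives, and it makes both indices uninformative about missed cases at any sample size.

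What is at stake is a figure of 100%, or close to it, in the final paper that reflects the referral rule and not the test. It would suggest that no affected child is missed. The limitations listed in section 4 do not mention that screen-negatives go unverified.

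**Working it through.** **Inputs.** From 2.2.1: 1,500 screened children and a frequency of 2–2.5%, with 9.2% the highest detection frequency in the review cited there. From 2.3.5: 37 disorders, which agrees with Table 3 (12 + 14 + 11 = 37). From 3.5: a false-positive rate of 1.9–2.3%, read here as a share of all screened children (an assumption). The 1,500 itself cannot be reproduced, because 2.2.1 gives no precision, but nothing below depends on how it was reached.

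**Step 1: which cells of the 2×2 table are filled.** TP and FP come from confirmatory work-up. FN and TN would have to come from screen-negative children, who receive none. Two ways of proceeding remain:

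- Count unverified negatives as disease-free. Then FN = 0, sensitivity = TP/(TP+0) = 100%, and NPV = TN/(TN+0) = 100%.
- Drop unverified negatives. Then FN = TN = 0, sensitivity is still 100%, NPV = 0/0 is undefined, and specificity = 0/(0+FP) = 0%.

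**Step 2: what could be hidden.** Expected cases are 1,500 × 0.02 = 30 to 1,500 × 0.025 = 37.5. Take 33 detected. The numbers missed are assumptions; the protocol gives none. False positives are 1,500 × 0.019 = 28.5, so 1,500 − 33 − 28.5 = 1,438.5 children screen negative.

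| Missed (assumed) | True sensitivity | Reported sensitivity | True NPV | Reported NPV |
|---|---|---|---|---|
| 5 | 33/38 = 87% | 100% | 1,433.5/1,438.5 = 99.7% | 100% |
| 10 | 33/43 = 77% | 100% | 1,428.5/1,438.5 = 99.3% | 100% |
| 15 | 33/48 = 69% | 100% | 1,423.5/1,438.5 = 99.0% | 100% |

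A confidence interval would give no warning. The exact lower 95% limit for 33/33 is 0.025^(1/33) = 89.4%, above all three true values.

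**Step 3: what survives.** PPV uses verified positives: 33/(33+28.5) = 54%, or 33/(33+34.5) = 49% at a false-positive rate of 2.3%. Specificity is barely affected. With unverified negatives counted as disease-free it is 1,438.5/(1,438.5+28.5) = 98.06%; with 15 of them in fact affected it is 1,423.5/(1,423.5+28.5) = 98.04%.

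**Step 4: cases per disease.** 30/37 = 0.81 and 37.5/37 = 1.01 on average. With equal shares, a given disorder has a 44% (at 2%) to 36% (at 2.5%) chance of no case. At 9.2% there would be 138 cases, and 138/37 = 3.7. A proportion of 1/1 has an exact 95% interval of 2.5% to 100%.

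**The case against.** Several points on the other side are sound.

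- **Not every test is fixed at 100%.** Section 3.2 speaks of each diagnostic test, which can include single markers, ratios and confirmatory tests. One marker can miss a child flagged by another, so its sensitivity can fall below 100%. That stands, but such a figure is relative to children whom the panel caught and says nothing about those it missed.
- **A false negative could surface by chance.** Exclusion 7 in 2.2.4 does not cover a child already diagnosed with one of the target disorders. If such a child were enrolled and screened normal, a miss would be seen. The protocol does not say that this will happen, and it would not be a systematic check.
- **The 750 healthy children.** They set the cut-offs. No confirmatory testing of them is described, so they cannot supply false negatives.
- **A separate analysis plan might settle it.** It could choose a convention, but it cannot create reference results that the work-up does not collect.

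A reader might infer more than the text supports:

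- **Sensitivity for every disorder.** Section 3.2 promises indices per test. Only the true and false positive counts in 3.5 are per disease.
- **Cut-offs tuned on the same children in whom accuracy is measured.** Section 2.3.4 derives limits from the healthy children and leaves them open to adjustment. Overlap is possible but not stated.
- **The national programme rests on sensitivity.** Section 4 ties the future panel to disease frequency, economic factors and laboratory equipment. Accuracy indices are absent from the study tasks and from the outcomes in 3.1.

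**Conclusion.** The point holds for sensitivity and NPV of the LC-MS/MS screen as a whole: they are not estimable under the described work-up. The figure of 100% for both assumes that unverified negatives are counted as disease-free; dropping them leaves sensitivity at 100% and NPV undefined. The true sensitivities of 87%, 77% and 69% illustrate assumed misses and do not predict them.

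PPV and the detection rate (cases diagnosed over children screened) do not need a verdict on negatives. Specificity need not be deleted, since its bias is about 0.02 percentage points in the worst illustrated case at this prevalence. The mean of 0.8 to 1.0 cases per disorder assumes 2–2.5%; actual cases will be unevenly spread.

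The defect sits in one sentence of 3.2 and does not touch the tasks or primary outcomes, but the sentence should be corrected before analysis.

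**What to change.** In section 3.2:

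1. Remove sensitivity and NPV of the LC-MS/MS screen. If sensitivity of a single marker or ratio is kept, label it as relative to verified panel-positive children.
2. Report the first-test positive rate, repeat-positive rate, false-positive rate, PPV and detection rate with exact 95% intervals, overall and for amino acid disorders, organic acidemias and fatty acid oxidation disorders.
3. If specificity is kept, state that it treats unverified negatives as disease-free and that the bias is small at 2–2.5% prevalence.
4. State that screen-negatives are unverified, and which cut-off version each index uses.
5. Give the per-disease results of 3.5 as counts.

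This changes wording only and needs no new data. The cost is that the final paper carries no sensitivity or NPV for the screen. If a sensitivity figure is wanted, a random sample of screen-negatives would have to be verified and the estimate corrected for verification bias. That is expensive for what it yields: even with 15 missed among 1,438.5 negatives, a sample of 100 would hold about one (100 × 15/1,438.5 = 1.04).
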